### Multi-component intervention (MCI)

Self-management is a process in which patients take responsibility for changing their health behavior by acquiring knowledge about their disease and treatment, and by managing symptoms as well as the physical and psychosocial consequences of the disease [27].

This definition is a compilation of a broad range of definitions about self-management, combining physical functioning and outcomes with knowledge and the psychosocial consequences of disease. Our MCI is based on this idea. In order to manage symptoms or the physical and psychosocial consequences, we will try to provide patients with knowledge about self-monitoring (by use of e-health tools) and risk management. In addition, in order to change behavior, emphasis will be put on proactive coping, concordance and goal-setting.

Patients will have the opportunity to bring one of their relatives/friends for social support, based on the fact that self-management is not only supported by healthcare providers, but also by the people surrounding persons with chronic diseases [27]. The intervention is based on the self-management intervention offered in the Restore4Stroke study [28] but was adjusted to make it suitable for epilepsy patients. The final version of the intervention was developed in agreement with experts in the field of self-management, coordinators of the Restore4Stroke study, clinicians, and representatives of the Epilepsy Association of the Netherlands (EVN, Epilepsie Vereniging Nederland).

The intervention will be explained in a detailed protocol for the NP offering the intervention in the outpatient clinic and in a workbook for patients and one of their relatives/friends. In addition, NPs will receive training beforehand on motivational interviewing (MI), as a technique to empower patients to set their own sustainable goals and look into conflicting beliefs. MI is defined as “a collaborative, person-centered form of guiding to elicit and strengthen motivation for change” [29]. MI focuses on exploring and resolving ambivalence and centers on motivational processes within the individual that facilitate change [30].

### Group sessions

The MCI is offered as a group treatment to groups of 5 patients and additional family members and/or friends. The MCI will last 9 weeks. During the first 5 weeks, group sessions will take place once a week, followed by a booster session 3 weeks later. The group sessions last 2-2.5 hours and are led by an NP with experience in working with epilepsy patient groups. The first session is aimed at providing information about the MCI, including materials, and getting to know the other participants and therapists. During the next sessions, participants will practice with the five stages of proactive coping defined by Aspinwall & Taylor [31]. These five stages are (1) resource accumulation, (2) recognition of potential stressors, (3) initial appraisal, (4) preliminary coping efforts, and (5) elicitation and use of feedback concerning initial efforts.

The model will be applied by the patients to three fixed epilepsy-related themes. The first theme will be self-monitoring and self-monitoring (e-Health) tools. The other two themes will be risk-management and shared decision-making/concordance.

Each group session will have the same basic structure. The sessions will begin by looking back at goals set in the previous meeting and how things have worked in the last week. Next, the theme of the session will be introduced. Patients and caregivers will be invited to share their beliefs, emotions and experiences with regard to the theme. Subsequently, patients and caregivers will formulate their own action plan in order to attain a goal relevant to the theme. Patients will be instructed to keep their goals feasible, and group members will give feedback on the quality of the goals in terms of concreteness and attainability. They will help each other to recognize additional conditions and barriers which need to be addressed. After the feedback discussion, patients and caregivers will formulate their final plan.

### e-Health

The e-Health tools used in the intervention consist of 3 elements: 1) the Medication Event Monitoring System (MEMS; Aardex Ltd., Switzerland), 2) a smartphone application, and 3) an internet accessible patient database. The MEMS caps are electronic caps that fit on standard pill bottles. They register the date and time every time the pill bottle is opened. In addition, the MEMS of the intervention group will include an LCD-screen which provides feedback on the number of times the bottle is opened on a particular day. These data can be downloaded from the MEMS cap by the researchers with a communication device and a computer. A computer program will then present the data in simple plots which can be used to provide feedback about behavior, and to identify sub-optimal adherence patterns [32]. Feedback will be provided during the MCI and during each follow-up visit. The smartphone application (“Eppy”; Epilepsy Foundation, the Netherlands) is designed to register seizure frequency and other facts for persons with epilepsy, in order to provide data which can influence the management of epilepsy. “Eppy” can be downloaded at no charge from the App store (Apple Inc., USA) or from the Google Play store (Google Inc., USA). The application provides patients with the opportunity, among others, to keep a seizure diary, to set reminders for the intake of medicines and an alarm mode in which a text will be shown for bystanders in case of a seizure. Data gathered with “Eppy” can be synchronized to an internet accessible database, which gives an overview of all clinical events registered by the patient. This internet website is owned by the patient, who can allow healthcare professionals to access it for clinical and research purposes.

### Booster session

During the booster session the NP will rehearse goal setting themes and other themes discussed in the group sessions. Patients and caregivers will have the opportunity to discuss their experiences related to their goals and other aspects of the intervention.

### Control group

The control condition will be a control condition with unrestricted access to CAU. Care will not be intensified after enrollment. As this will be a pragmatic trial, CAU will not follow a standardized protocol. However, medical support will be documented in the electronic patient file of each patient. Medical support provided in the control group might be variable, but is expected to be in agreement with the standard epilepsy guidelines (i.e. preference for mono-drug therapy, a monitoring visit every 4 months by neurologist or epilepsy nurse and change or addition of medication if the first AED is ineffective) [33]. The control group will receive MEMS but without feedback about their behavior. The MEMS will be read only at the end of the follow-up as a way to measure adherence and will not include an LCD-screen.


**Table 1 Tab1:** **Overview of measurements per time point**

**Outcomes patients**	**Instrument**	**Short term**	**T0**	**T1**	**T2**	**T3***	**T4***
Demographic and clinical characteristics	-	**-**	X	**-**	**-**	**-**	**-**
Self-efficacy	Epilepsy Self-efficacy Scale – 33 items	ESES	X	X	X	X	X
General self-efficacy	Generic Self-efficacy Scale – 10 items	GSES	X	X	X	X	X
Adherence	MEMS Medication Adherence Scale	MARS 5	X	X	X	X	X
Seizure frequency	Questionnaire seizure frequency	-	X	X	X	X	X
Seizure severity	National Hospital Seizure Severity Scale	NHS3	X	X	X	X	X
Emotional functioning	Hospital Anxiety and Depression Scale	HADS	X	X	X	X	X
Quality of life	Quality Of Life in Epilepsy	QOLIE31P	X	X	X	X	X
	Generic quality of life	EQ-5D-5L	X	X	X	X	X
Proactive coping	Utrecht Proactive Coping Competence	UPCC/PCI	X	X	X	X	X
Side effect	Side effects of Anti-epileptic Drugs	SIDAED	X	X	X	X	X
Healthcare resource use	Medical Cost Questionnaire	MCQ	X	X	X	X	X
	Productivity Cost Questionnaire	PCQ					

T0 = baseline outcome assessments; T1 = Outcome assessments after 3 months; T2 = Outcome assessments after 6 months; T3 = Outcome assessments after 9 months; T4 = Outcome assessments after 12 months.

*Outcome assessment applicable only for intervention group.

## Economic evaluation

The trial-based economic evaluation will be performed from a societal perspective and will consist of a cost-effectiveness analysis (CEA) and a cost-utility analysis (CUA). Outcomes of interest for the CEA and the CUA will be self-efficacy as assessed by the ESES, and generic quality of life as assessed by EQ-5D-5L. We distinguish four cost categories: intervention costs, healthcare sector costs, costs for the patient and family, and productivity costs. Intervention costs will be defined as all costs related to the MCI including travel costs, personal costs, material costs, costs of e-Health tools (i.e. MEMS) and housing costs. Healthcare and patient costs will be estimated using a questionnaire regarding healthcare resource utilization and productivity losses.

Resource use and outcomes are measured at the same time points mentioned in the effectiveness study: at baseline, 3 months, 6 months, 9 months, and 12 months in the intervention group and at 3 months and 6 months in the control group. A comparison between MCI and CAU will be made in terms of incremental costs and incremental effects. The time horizon will be 12 months (trial-based economic evaluation). To measure the use of health care resources, including all activities related to epilepsy, we gather data for each patient at baseline and at a follow-up of one year. Cost calculations will be based on the Dutch guidelines for cost calculations in healthcare [47].

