## Design

A randomized controlled trial (RCT) with two parallel groups will be conducted to compare the MCI with a control situation in epilepsy patients. Patients assigned to the intervention group will attend the MCI consisting of five weekly sessions and one booster session. The control group will receive CAU as naturally as possible. The follow-up of patients in the intervention group will be 12 months and the follow-up of patients assigned to the control group will be 6 months, after which patients in the control group have the opportunity to receive the MCI outside the study (see Figure 1). The study has been approved by the Ethics Committee of University Hospital Maastricht, the Netherlands.

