## Analysis

### Clinical effectiveness

Baseline characteristics will be described, and differences between groups at baseline will be studied using t-tests or chi-square tests where appropriate. All statistical procedures will be conducted based on both the intention-to-treat principle and on actual participation in treatment (i.e. effectiveness analyses) and will be performed using SPSS statistics 22.0 (SPSS, IBM, Corporation, Chicago, USA). Missing data will be handled using SPSS missing value analysis on item level. Completely missing measurements will be handled using multiple imputation. To evaluate outcomes, change scores will be calculated and compared between the groups after treatment. Multi-level analyses will be performed with measurements (T0, T1, T2, T3 and T4) within the subjects’ factor and group and between subjects’ factors to account for the nested structure of the data. Data from the control group will be extrapolated to 12 months. Post hoc analyses will be performed in case of significant effects. Baseline differences will be corrected by inclusion of covariates in the analyses. A 2-sided significance level of 0.05 will be used as a threshold to determine whether differences are statistically significant.

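### The economic evaluation is called trial-based over 12 months, but controls are followed for 6 months, and the rule for extending their data is neither stated nor varied.

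*Protocol article*

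**What the plan says.** All references are to the protocol article.

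- **Economic evaluation (horizon and data).** "The time horizon will be 12 months (trial-based economic evaluation"), for a comparison of MCI with care as usual (CAU). On health care use, the section says "we gather data for each patient at baseline and at a follow-up of one year". Just before, it lists the intervention arm at baseline and at 3, 6, 9 and 12 months, but measurement only "at 3 months and 6 months in the control group".
- **Design.** "The follow-up of patients in the intervention group will be 12 months", whereas "the follow-up of patients assigned to the control group will be 6 months". After that, "patients in the control group have the opportunity to receive the MCI outside the study".
- **Table 1.** The 9- and 12-month columns (T3, T4) carry the footnote "Outcome assessment applicable only for intervention group". Baseline (T0) has no such limit.
- **Analysis, Clinical effectiveness.** "Data from the control group will be extrapolated to 12 months". No method is given.
- **Analysis, Economic evaluation.** QALYs come from the area under the curve. Uncertainty is shown by bootstrapping, a cost-effectiveness plane and an acceptability curve. One-way and multi-way sensitivity analyses are planned for the main cost parameters. Extrapolation is not mentioned here.

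**The concern.** A trial-based comparison over 12 months needs 12 months of data in both arms. Here one arm has them and the other stops at month 6. The sentence promising one-year data for each patient cannot be true of controls under the stated design.

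The missing half-year cannot be recovered later from the trial either. Controls who take up the MCI after month 6 no longer represent CAU. The cost questionnaires each look back 3 months, so even an unplanned form at month 12 would leave months 6 to 9 uncovered.

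At stake is the answer to the cost-effectiveness question, one of the study's three parts. Every 12-month economic result would depend on a rule that readers cannot see and that no planned sensitivity analysis varies. Bootstrapping under one rule shows sampling variation given that rule. It does not show uncertainty about the rule.

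**Working it through.** The 12-month horizon is a design choice, so there is no plan figure to reproduce. The check compares the horizon with the observation window and then asks how far the control rule can move the QALY result.

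**Step 1. Share of control time without data.** Inputs: horizon 12 months (Economic evaluation), control follow-up 6 months (Design), 50 patients per arm (Sample size).
- Control arm: (12 − 6)/12 = 50%. In planned patient-months before dropout, 50 × 12 = 600 and 50 × 6 = 300 are observed, so 300 are not.
- Both arms: 300/1200 = 25%.
- With a 6-month horizon, all control time is covered by T0, T1 and T2.

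**Step 2. Weight of that time in the QALY.** With assessments at 0, 3, 6, 9 and 12 months, the trapezoidal weights in years are 0.125, 0.25, 0.25, 0.25 and 0.125. The segment from month 6 to month 12 has length 0.5 year. An error d in the assumed mean control utility over that segment therefore shifts the incremental QALY by 0.5 × d:
- d = 0.01 gives 0.005
- d = 0.02 gives 0.010
- d = 0.05 gives 0.025

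**Step 3. Effect of the rule, illustrated.** The article gives no utilities, so these are assumptions chosen only to show the mechanism. Intervention: 0.80, 0.82, 0.84, 0.84, 0.84 (all five would be observed). Control to month 6: 0.80, 0.805, 0.81.

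Intervention 12-month QALY: 0.125×0.80 + 0.25×0.82 + 0.25×0.84 + 0.25×0.84 + 0.125×0.84 = 0.8300.

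| Rule for controls | Months 9, 12 | Control QALY | Gain |
|---|---|---|---|
| Converge to intervention values | 0.84, 0.84 | 0.81875 | 0.01125 |
| Linear trend continues | 0.815, 0.82 | 0.8100 | 0.0200 |
| Month-6 value carried forward | 0.81, 0.81 | 0.8075 | 0.0225 |
| Return to baseline | 0.80, 0.80 | 0.80375 | 0.02625 |

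The largest gain over the smallest is 0.02625/0.01125 = 2.33. At a fixed incremental cost, the ICER would move by the same factor. Incremental costs would also depend on a rule, because control costs after month 6 are unobserved too.

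Over the first 6 months the same inputs give 0.4100 − 0.4025 = 0.0075, and no control value in that figure needs extrapolation.

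**The case against.** The strongest reply is that the article discloses the extrapolation. It does so under clinical effectiveness, but EQ-5D-5L utilities and societal costs are listed among those outcomes, so the sentence can fairly be read to cover them. A condensed article may also leave the exact rule to a fuller plan. This stands: a reader might infer that the gap is hidden, and it is not. What remains is the trial-based label, the false one-year sentence, and sensitivity analyses limited to cost parameters.

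Other tempting inferences go too far:

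- *Control QALYs for months 0 to 3 cannot be computed.* The economic section omits baseline from the control time points, but it also refers to the time points of the effectiveness study and says each patient has baseline data. Table 1 has T0 for both arms. This is a wording slip.
- *The ICER halves purely by assumption.* A constant gain u yields 0.5u QALY in 6 months and 1.0u in 12, but that comes from the longer horizon and would occur with full control follow-up. The intervention arm is measured to month 12, so its persistence is observed. The relevant measure is the spread across control rules at 12 months, as in Step 3.
- *Half of control costs and QALYs are assumed.* Half is exact for time. For costs and QALYs it holds only if they accrue evenly.
- *The bootstrap will treat extrapolated values as data.* The article does not say whether extrapolation precedes resampling or is repeated within each replicate. In either case, a single rule leaves uncertainty about the rule unshown.

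It is also fair to say that a 6-month view sets a 9-week programme's cost against only half a year of benefit. That is a reason to keep a 12-month result, properly labelled.

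**Conclusion.** The point holds as a mismatch between horizon and follow-up, with one sentence that contradicts the design. Half of the control arm's time within the horizon (300 of 600 planned patient-months) rests on an unstated rule, and the planned sensitivity analyses leave that rule alone. The shift of 0.5 × d in the incremental QALY follows from the assessment schedule. The 2.33-fold spread depends on assumed utilities and shows only that the rule can matter a great deal. The spread in the actual trial could be smaller or larger.

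This should be fixed before analysis. It is not more serious than that, because the extrapolation is disclosed, the data for a valid 6-month comparison are already planned in both arms, and the economic evaluation is a separate part of the study.

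**What to change.** 1. Report the 6-month comparison (T0 to T2, both arms measured) as the trial-based cost-effectiveness and cost-utility result.
2. Present the 12-month result as extrapolation and label it so. Use the observed intervention data to month 12 and at least two stated assumptions for control costs and utilities, for example month-6 values carried forward, and controls converging to the observed intervention values. An assumption that the effect vanishes needs to be specified in this second way, since the intervention values are observed.
3. Extend the sensitivity analyses to that assumption, and show the plane and acceptability curve under each rule.
4. Reword the one-year data sentence to match the 6-month control follow-up, and add baseline to the list of control time points.

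The cost is some rewording and a small amount of extra analysis, with no new data collection. The downside is a shorter horizon for the result that carries the trial-based label.

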## Process evaluation

Process evaluation will be performed to assess whether the MCI was delivered according to protocol, to examine the experiences and opinions of patients, caregivers and professionals regarding the MCI, and to determine to what extent the MCI has impacted concordance among patients. The process evaluation will be performed according to the framework provided by Saunders et al. [48]. This framework consists of a stepwise approach in which important characteristics for the process-evaluation plan are identified along seven basic components, namely: fidelity (quality), dose delivered (completeness), dose received (exposure), dose received (satisfaction), reach (participation rate), recruitment and context.

We will use a mixed methods design in which both qualitative and quantitative data will be collected. The qualitative part will consist of observations during several group sessions over time. After each observation, a short interview will be held with the group leader(s) in which the group leader can reflect on his/her opinion regarding the session. During the last (sixth) group session of every MCI-group, a short evaluation form will be handed out to patients in which they will be asked to rate different aspects and themes of the MCI on a 7-point Likert scale. Furthermore, at the end of the study, focus groups will be held consisting of patients included in the study. The selection of participants will be based on maximal variation to get as many perspectives as possible. Participants will be selected based on age, sex and severity of seizures and effectiveness of the intervention (to compare patients for which the intervention was successful versus unsuccessful). Focus groups will be conducted using a semi-structured questionnaire covering the topics identified in the framework provided by Saunders et al. [48].

## Analysis

### Clinical effectiveness

Baseline characteristics will be described, and differences between groups at baseline will be studied using t-tests or chi-square tests where appropriate. All statistical procedures will be conducted based on both the intention-to-treat principle and on actual participation in treatment (i.e. effectiveness analyses) and will be performed using SPSS statistics 22.0 (SPSS, IBM, Corporation, Chicago, USA). Missing data will be handled using SPSS missing value analysis on item level. Completely missing measurements will be handled using multiple imputation. To evaluate outcomes, change scores will be calculated and compared between the groups after treatment. Multi-level analyses will be performed with measurements (T0, T1, T2, T3 and T4) within the subjects’ factor and group and between subjects’ factors to account for the nested structure of the data. Data from the control group will be extrapolated to 12 months. Post hoc analyses will be performed in case of significant effects. Baseline differences will be corrected by inclusion of covariates in the analyses. A 2-sided significance level of 0.05 will be used as a threshold to determine whether differences are statistically significant.

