### Sample size

The primary outcome variable of this study will be self-efficacy as measured on the Epilepsy Self-Efficacy Scale 33 (ESES) [26]. In a previous pilot study exploring the effects of a psychosocial self-management program for epilepsy patients, with self-efficacy as the primary outcome, the difference between groups was approximately 10 points, with a standard deviation of 7 points on the ESES [20]. Assuming that alpha = 0.05 and power p = 0.90, a minimally detectable difference of 5 points between the intervention and control groups, we will need to include 42 patients per group. Based on a dropout rate of 20% we intend to include 50 patients in each group.

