### Randomization

Patients will be randomized to the MCI (intervention group) or to the control group, in which patients will be given the opportunity to attend the MCI outside of the study after six months of follow-up. For parallel provision of both groups (intervention & control), two blocks of five patients are needed at the moment of randomization. Patients will be assigned to the intervention group or the control group by means of block randomization, using blocks of 10 patients. An assistant who is not involved in the treatment nor in the trial will execute the procedure with a randomization program (www.randomization.com).

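### The MCI is given in interactive groups of five, but neither the sample size nor the stated model allows for correlation within those groups; any positive correlation makes the standard error too small and the power overstated

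*Protocol article*

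**What the plan says.** The relevant statements are in four sections of the protocol article.

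- **Group sessions:** "The MCI is offered as a group treatment to groups of 5 patients", with relatives or friends. A nurse practitioner leads the sessions, and members comment on each other's goals and help to identify barriers.
- **Randomization:** patients are randomised individually, "using blocks of 10 patients", so that five intervention and five control patients start in parallel. Under Design and Control group, controls receive care as usual and no group programme.
- **Sample size:** "Assuming that alpha = 0.05 and power p = 0.90", "a minimally detectable difference of 5 points between the intervention and control groups" and a pilot result "with a standard deviation of 7 points on the ESES", the plan concludes that "we will need to include 42 patients per group", raised to 50 for 20% dropout. It mentions no intraclass correlation, cluster size or design effect.
- **Analysis, Clinical effectiveness:** "Multi-level analyses will be performed with measurements (T0, T1, T2, T3 and T4") as the within-subject factor and group as a between-subject factor. The sentence presents this as dealing with nesting in the data. It names no term for the MCI group or its leader. The test is two-sided: "A 2-sided significance level of 0.05 will be used as a threshold".

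**The concern.** Interaction between members is part of this treatment, and the primary outcome, self-efficacy, is what the sessions aim to change. Patients in one MCI group share a leader and influence each other; control patients have no such grouping. This is a partially nested design: clustering arises after randomisation, in one arm only.

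A positive correlation within MCI groups raises the variance of the intervention mean above what a model with only visits within patients would estimate. The confidence interval for the arm difference is then too narrow, the type I error exceeds the stated 5%, and the power is below the stated 90%. The error runs towards declaring the MCI effective. The plan invokes nesting but names only one of the two kinds present.

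**Working it through.** **Inputs from the article.** Two-sided alpha 0.05, power 0.90, difference 5, SD 7, 42 per group before dropout, 50 per group planned with 20% dropout, MCI groups of 5. Hence 50/5 = 10 MCI groups.

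**Assumed.** The ICC within MCI groups is not given; 0.01 to 0.20 is used. Like the plan's own calculation, the check is a single comparison of two means, by normal approximation.

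**Step 1: reproduce the plan's figure.** For independent patients, n = 2 × [(1.960 + 1.282) × 7/5]² = 41.2, rounded up to 42 per group. This matches the article, so the design effect used was 1. A one-sided alpha would give 34. With 42 per group and no clustering, SE = 7 × √(2/42) = 1.528 and power = Φ(5/1.528 − 1.960) = 90.5%.

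**Step 2: add clustering in the intervention arm only.**

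- Design effect: DE = 1 + (m − 1) × ICC, where m is the number analysed per MCI group.
- Variance ratio against the independent case: R = (DE + 1)/2.
- True SE = 7 × √((DE + 1)/n).
- Power = Φ(5/SE − 1.960).
- Type I error if clustering is ignored = 2 × [1 − Φ(1.960/√R)].

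With 42 analysed in 10 groups, m = 42/10 = 4.2:

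| ICC | DE | R | True/naive SE | Power | Type I error |
|---|---|---|---|---|---|
| 0 | 1.000 | 1.000 | 1.000 | 90.5% | 5.0% |
| 0.01 | 1.032 | 1.016 | 1.008 | 90.1% | 5.2% |
| 0.05 | 1.160 | 1.080 | 1.039 | 88.3% | 5.9% |
| 0.10 | 1.320 | 1.160 | 1.077 | 86.0% | 6.9% |
| 0.20 | 1.640 | 1.320 | 1.149 | 81.3% | 8.8% |

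Example at ICC 0.05: DE = 1 + 3.2 × 0.05 = 1.16; R = 2.16/2 = 1.08; SE = 7 × √(2.16/42) = 1.588; power = Φ(3.150 − 1.960) = 88.3%.

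**Step 3: after the planned dropout.** 50 × 0.8 = 40 per arm, so m = 4. Power is 89.1% without clustering, 86.9% at ICC 0.05 (DE 1.15) and 84.6% at ICC 0.10 (DE 1.30).

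**Step 4: what the ICC must represent.** Because the arms start in parallel within a block of 10, site and calendar time are largely common to both arms and cancel in the difference. Let c be the correlation specific to MCI groups and b the share of variance due to effects common to the whole block. The intervention arm contributes 1 − b + (m − 1)c and the control arm 1 − b, so R = 1 − b + (m − 1)c/2. With m = 4.2 and c = 0.05, R = 1.08 − b: 1.08 if b = 0, 1.03 if b = 0.05, and 1.00 if b = 0.08. The table is the case b = 0.

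**The case against.** The strongest objections, and what remains of each:

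- **The direction depends on the correlation.** No ICC is given, and at 0.01 the effect is negligible. This stands. A reader might infer that the standard error is certainly too small; the document supports this only if leader and peer effects produce a positive correlation. A shared leader and planned member interaction make that plausible but do not fix its size.
- **Site, calendar time and block.** A reader might add site and calendar time to the causes, or infer that leaving the block out of the model also narrows the intervals. The Randomization section does not support either. Both arms start in parallel in blocks of 10, so those effects are largely shared with controls. Omitting a block term balanced across arms makes the naive standard error, if anything, too large. As step 4 shows, this can offset part or all of the inflation.
- **A condensed article may leave random effects to a fuller plan.** This has some force for the model: the analysis sentence is loosely worded, and reading its word for group as trial arm is an inference, though the natural one, since the preceding sentence compares change scores between the arms. Even if it meant the MCI group, a between-subject factor is not a random effect confined to one arm. The objection does not reach the sample size, a fixed figure that reproduces exactly under independence.
- **Few groups.** About 10 groups give a poor estimate of the group variance. This stands as a drawback of the remedy, and it also means that resampling whole groups in the economic bootstrap would be unreliable, so that is not proposed.

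**Conclusion.** The point holds in conditional form. The 42 per group makes no allowance for group delivery, and the model as worded names no MCI-group level. Both rest on independence between patients who are treated together.

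If within-group correlation from leader and peer effects is positive and not offset by shared block effects, the cost at 42 per arm ranges from nothing of practical note (ICC 0.01) through about 2 points of power and a 5.9% type I error (0.05) to about 9 points and 8.8% (0.20). One-arm clustering in small groups keeps the loss moderate. The sample-size part is certain; the model part rests on the natural reading of one sentence. The size rests entirely on assumed ICCs. The change is worth making because it is cheap and the possible error favours the intervention.

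**What to change.** - **Analysis, Clinical effectiveness:** add a random effect for MCI session group in the intervention arm only, treating each control as a group of one, alongside the existing level for visits within patients. Use small-sample degrees of freedom, as there are only about 10 groups. State explicitly that group as a between-subject factor means trial arm.
- **Sample size:** declare an ICC range and restate the power under it, using the number expected to be analysed per MCI group after dropout.

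Group membership is known from delivery of the programme, so no new data are needed. The cost is slightly wider intervals, a stated power somewhat below 90%, and a group variance that about 10 groups estimate imprecisely, which should be acknowledged when results are reported.
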